## Abstract

**Background:**

Substance use disorder (SUD) is associated with executive function (EF) deficits and sensory modulation dysfunction (SMD). Yet, these deficits are not addressed therapeutically. This study aims to examine the effectiveness of the Functional-Cognitive and Sensory Treatment (F-CaST) compared to standard care to improve everyday performance and behavior and length of stay at the therapeutic community (TC) in individuals with SUD. In addition, to assess the improvement in EF, sensory modulation, participation, self-efficacy, life satisfaction, and use of strategies within and between groups. Satisfaction with F-CaST will also be assessed.

**Methods:**

Forty-eight participants from a community of men in a TC, aged 18–45 years will be randomly allocated to (i) F-CaST—(experimental group) providing sensory and EF strategies for improving daily function; (ii) standard care (control group) as provided in the TC. Assessments will be conducted by assessors blind to group allocation at 4 time points: T1- pre-intervention; T2- post-intervention; T3- 1-month follow-up; and T4- 3-month follow-up. Primary outcome measures will be everyday performance, assessed by the Canadian Occupational Performance Measure (COPM), behavior and length of stay in the TC; secondary outcome measures will assess EF, SMD. Semi-structured in-depth qualitative interviews will be conducted at T1, T2 and T4.

**Discussion:**

We hypothesize that F-CaST will lead to improved everyday performance and longer length of stay in the TC, compared to the control group. If F-CaST will prove to be effective, cognitive and sensory strategies may be incorporated as an adjunctive intervention in SUD rehabilitation.

*Trial registration*: ClinicalTrials.gov NCT05647863 Registered on 13 December 2022, https://classic.clinicaltrials.gov/ct2/show/NCT05647863.

## Background

Substance use disorder (SUD) is an urgent public health concern characterized by cognitive, behavioral, and physiological symptoms due to uncontrolled use of psychoactive substances despite harmful consequences. SUD severely impacts every life domain [1]. According to the National Survey on Drug Use and Health (2020), 58.7% of the US population aged 12 or older reported to use tobacco, alcohol, or an illicit drug in the past month. Of these, approximately 14.5% (40.3 million) are diagnosed with SUD [2], a two-fold increase compared to the previous year. In Israel rates are even higher, comprising 19.4% [3]. SUD has significant consequences across multiple life domains (e.g., work, school, home) and widespread ramifications in areas such as health (e.g. organ damage, infection, trauma or death) and society (crime, violence including domestic violence, and child abuse) [2]. It is an urgent public health concern with devastating effects that not only may persist across generations, but also cause a significant economic burden [4], estimated as more than $700 billion annually in the US [5].

Cumulative studies have demonstrated that SUD is associated with diverse cognitive impairments in attention, memory and executive functions (EF) [6, 7]. Importantly, although there are different profiles linked each to a specific type of substance, memory and EF are recognized as converging areas of deficit across different substance [6]. EF is an umbrella term comprising interrelated sets of abilities that direct and coordinate cognitive control. These are supported by dynamics of a superordinate, spatial distributed brain networks [8], allowing to perform rational decisions and emotion regulation, which contribute to efficient functioning and quality of life [9, 10]. The repeated use of substances leads to abnormal neural activity [11],related to learning and reward [12], and including the amygdala, hippocampus and prefrontal cortex. Indeed, a high prevalence of EF deficits have been reported to be present in SUD patients (53–70%) [13, 14], although it is controversial as to whether deficits in EF are a cause [15] or a consequence of SUD.

EF have been recognized as a key predictor for effective goal achievement and high self-efficacy, and therefore intact EF are crucial for treatment compliance and rehabilitation success [7, 16, 17]. Evidence clearly demonstrates that deficits in EF reduce successful SUD rehabilitation, specifically of cognitive behavioral therapies commonly provided in SUD rehabilitation programs [6, 13]. Indeed, dropouts, especially from long-term treatment frameworks, were recognized as a serious challenge in the treatment of SUD [13, 18]. Specifically, the estimated therapeutic community (TC) dropout rates stands up to 71% [18, 19], emphasizing that EF should be an important neurocognitive target in SUD interventions. Importantly, a recent systematic review concluded that cognitive remediation has the potential to pave the avenue for improving cognition and treatment outcomes in SUD [6].

Information processing that underlies EF is directly related to sensory perception. EF, specifically inhibitory control, plays an important role in the way sensory input from the environment is processed [20, 21]. Although deficits in EF have been found to be associated with difficulties in sensory processing within various populations across the life span (e.g., children with Autism Spectrum Disorders [21]; attention deficit hyperactivity disorder (ADHD); adults with specific learning disabilities [24] and older adults [25], there is limited research regarding populations with SUD. We have recently reported Sensory modulation dysfunction (SMD) in 54% of individuals with SUD (*vs.* 11.7% in a healthy comparison group) and revealed that sensory over-responsivity is a major contributing factor in SUD phenomenon [25].

SMD is a neuro-developmental condition, characterized by difficulty in regulating the degree, nature, or intensity of sensory stimulation in an adaptive manner [26, 27], consequently interfering with participation in everyday activities [28, 29] and quality of life [30–32]. The estimated prevalence of SMD is 5%-16% in the healthy general population [25, 33, 34]. Research studying the underlying mechanisms of SMD suggests alterations in neural processes [35–41] and anatomical abnormalities in sensory pathways [42] that may contribute to behavioral manifestations of sensory under- or over-responsivity. Sensory under-responsivity is manifested by disregarded or delayed responses to sensory stimulation, while sensory over-responsivity is characterized by experiencing non-painful sensations as irritating, unpleasant [26, 43] or painful [44].

Importantly, despite the fact that deficits in EF and SMD are common in SUD and have a substantial clinical relevance [45], as far as we know, there is no intervention combining both for individuals with SUD. Moreover, the majority of existing cognitive intervention programs used in SUD are restorative (or “bottom-up”) approaches [46], and their effectiveness have been tested using neuropsychological assessments and not by performance-based assessments [43, 45]. Our novel intervention, the Functional-Cognitive and Sensory Treatment (F-CaST) aims to bridge these gaps targeting the improvement of occupational performance, as has been recently suggested [48]. The F-CaST is an occupational therapy intervention aiming to provide cognitive and sensory strategies for improving daily functioning within the TC. The F-CaST teaches participants *“how to”* (vs. the more traditional virtue of “*what to*”). We based the F-CaST on the Functional and Cognitive Occupational Therapy (FaC_o_T) intervention, which was found to be effective in improving daily performance [49] and increasing self-efficacy [50] in adults with mild stroke. In addition, the F-CaST is based on The Ecological Model of SMD [51], which embraces the environment as a critical factor and recognizes the interplay between sensation, attention and emotion, which are linked to EF. Therefore, this proposed research aims to provide F-CaST, a novel intervention to improve rehabilitation outcomes for individuals with SUD living in a Therapeutic Community (TC).

We are planning to conduct a single-blind randomized-controlled clinical trial to determine whether the F-CaST is more effective than standard care for improving (1) everyday performance and (2) behavior and length of stay in the TC.

In addition, we aim to assess the improvement in EF, sensory modulation, participation, self-efficacy, life satisfaction, and use of strategies within each group and to compare between groups. For individuals in the F-CaST group, we aimed to evaluate their satisfaction with the intervention.

## Methods

A mixed-methods approach will be used; a single-blind randomized controlled trial comparing the F-CaST (experimental group) to standard care (control group) and a qualitative investigation (See Fig. 1).

**Fig. 1 Fig1:**
[figure not shown]
Mixed-methods approach; see the Quantitative and Qualitative outcome measures. This should appear below the Figure: T1- pre-intervention; T2- post-intervention; and T4- 3-month follow-up; COPM- Canadian Occupational Performance Measure; TC- Therapeutic Community; CTT- Color Trails Test; BRIEF-A- Behavior Rating Inventory of Executive Function-Adult Version; SRQ-IS-The Sensory Responsiveness Questionnaire-Intensity Scale; SE-Self Efficacy; NGSE- The New General Self-Efficacy Scale; SRSI- The Self-Regulation Skills Interview

Assessments will be conducted at four time points: T1 pre-intervention; T2 post-intervention; T3 one-month follow-up; and at T4 3-month follow-up, by assessors blinded to group allocation (See Fig. 2). Assessors are licensed occupational therapists, who are trained to administer and score all of the assessments. This study design will allow to identify changes in performance due to the intervention and verify whether the changes are stable. Since high dropout rates have been reported, repeated follow-up assessments are important. In addition, a qualitative investigation including in-depth interviews with the participants will be conducted to provide a deeper understanding of their perceived deficits and how these impact their everyday performance and treatment compliance in the TC (See Fig. 1).

**Fig. 2 Fig2:**
[figure not shown]
CONSORT Flow Diagram

Prior to the RCT we will conduct a prospective observational study with 4-point assessments including a group of individuals with SUD, receiving no additional treatment. This group of participants, although not randomized will form an additional control group.

## Setting

An adult community of men, within a TC. The TC is a rehabilitation center providing a controlled drug free environment with multidimensional support for individuals with severe SUD. Treatment in the TC is hierarchal, based on the duration and progress of the residents and usually lasts 1–1.5 years. The abstinence of the residents is routinely verified through random urine testing**.** Only individuals with the diagnosis of severe SUD (drug and/or alcohol use) and with no dual diagnosis are accepted into this TC. Diagnoses is done by a psychiatrist according to the Diagnostic and Statistical Manual of Mental Disorders-IV (DSM-IV).

## Participants

Forty-eight men with severe SUD residing in a TC will be recruited into the RCT. This study will recruit only men (a majority at the TC) and as an attempt to eliminate confounding factors. There is accumulating evidence of sex differences in SUD etiology and clinical manifestation (biological aspects, seeking treatment, consumption patterns) [52, 53].

### Inclusion criteria

Men will be eligible to take part if they meet the following inclusion criteria: Aged 18–45 years; Adequate language skills; Abstained from drugs and alcohol for at least 21 days (verifying minimum withdrawal effects); No more than 21 days of TC residency (ensuring acquaintance with the facility requirement and framework); With no dual diagnosis; Without a significant cognitive deficit [according to the Montreal Cognitive Assessment (MoCA) ≥ 19/30 points) a valid and reliable tool to assess cognition among patients with SUD [54, 55]]; Without other neurological conditions.

### Sample size

The sample size was calculated to (i) detect a minimally clinically important difference of the primary outcome measure of everyday (occupational) performance (COPM; see below) with 80% power and a significance level of 0.05, and (ii) to account for a 40% dropout. Thus 24 participants per group will be recruited providing a total of 48 participants for the study**.**

### Quantitative outcome measures

#### Primary outcomes measure

Every-day performance in the TC; Behavior and length of stay in the TC.

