### Canadian Occupational Performance Measure (COPM) [56].

COPM is a semi-structured interview to capture the participant’s self-perception of everyday performance. Using 10-point scale participants are asked to identify and rate their performance and satisfaction from performance of three specific goals. The COPM has been found sensitive to change in the perceived occupational performance [57] and as a reliable and valid assessment for people with varied health conditions [58–60]. The COPM has been translated into Hebrew and used in other studies to assess daily performance e.g., [48, 49].

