### Behavior and length of stay in TC

Information regarding participant behavior (discipline, number of times being late for scheduled activities) will be collected from the TC counselors. Length of stay (days) residing in TC. The Longer time spent in the TC, the better**.**

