## Data analysis

Descriptive statistics will be used to describe the participants in each group, in terms of their, demographic information and SUD parameters, primary and secondary outcome measures. Pre-intervention differences between the two groups will be analyzed using t-Test for independent samples (continuous measures) or Chi square (dichotomous measures). A repeated measures ((2)X4) analysis of variance ANOVA will be used to compare within- and between- group scores, for time (T1, T2, T3, T4) comparing the F-CaST to standard care and for interaction time*group effect.

To assess the clinical meaningfulness of the outcomes, the Partial Eta squared in ANOVA effect size will be calculated. Partial Eta squared is interpreted as the proportion of the total variability in the dependent variable that is accounted for by variation in the independent variable. ANOVA Partial Eta squared of 0.01, 0.06 and 0.14 are considered small, medium and large effect sizes (respectively).

Statistical significance will be set at p < 0.05, and all analyses will be conducted using SPSS for Windows version 27.0 (SPSS Inc, Chicago, IL). The transcripts of each of the four in-depth interviews will be analyzed using content analysis (an initial review, the development of mapping categories, and the building of a mapping categories tree) [77].

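### Three unranked primary outcomes share one 0.05 threshold with no success rule, while the stated power and N = 48 rest on the COPM alone

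*Protocol article*

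**What the plan says.** The protocol article identifies its primary outcomes in several places, and the sets differ.

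- **Primary outcomes measure:** "Every-day performance in the TC; Behavior and length of stay in the TC".
- **Abstract, Methods:** "Primary outcome measures will be everyday performance, assessed by the Canadian Occupational Performance Measure (COPM), behavior and length of stay in the TC". This is a list of three, without ranking.
- **Background, closing aims:** the trial is to show an advantage for "improving (1) everyday performance and (2) behavior and length of stay in the TC", which is two numbered aims.
- **Abstract and main Discussion:** the hypothesis covers everyday performance and length of stay. Behavior is left out, and the text does not say whether both outcomes must improve.
- **Sample size:** 24 per group is set to "detect a minimally clinically important difference of the primary outcome measure of everyday (occupational) performance", by COPM, with 80% power at 0.05 and a 40% dropout allowance. No other outcome enters, and no visit is named.
- **Data analysis:** "Statistical significance will be set at p < 0.05". The paragraph describes a two-group by four-visit repeated-measures ANOVA, with no order of testing, division of alpha or definition of trial success.

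Two of the primary outcomes have more than one part. In the COPM, participants "identify and rate their performance and satisfaction from performance of three specific goals". For behavior: "Information regarding participant behavior (discipline, number of times being late for scheduled activities) will be collected from the TC counselors".

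**The concern.** A primary outcome carries the confirmatory claim, so a reader must know beforehand which result, or which combination, makes the trial positive. With three candidates at equal rank, one threshold and no rule, the authors could report success on whichever outcome crosses 0.05, and the 5% error rate would then not apply to the trial's main conclusion.

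The same gap affects power. The 80% figure applies to one COPM comparison at 0.05. Behavior and length of stay have primary status with no stated power. Any conventional division of alpha would also lower the power for the COPM itself.

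**Working it through.** **Inputs.** From the protocol article: three primary outcomes (abstract; Primary outcomes measure), or two if the numbered aims are counted (Background); threshold 0.05 (Data analysis); 24 per group, 80% power, alpha 0.05, 40% dropout (Sample size); 1:1 allocation (Randomization). Assumed, because not stated: two-sided tests, and a two-sample t-test as the basis of the sample size.

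**1. The plan's own figure.** Completers per arm: 24 × (1 − 0.40) = 14.4. In reverse, 14 / 0.60 = 23.3, which rounds up to 24. The stated N is therefore consistent with 14 completers per arm. It cannot be reproduced independently, because the article gives neither the minimally important COPM difference nor its standard deviation. Back-solving a two-sided t-test for 80% power gives a standardized difference of 1.10 with 14 completers per arm, or 1.08 with 14.4.

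**2. Error rate if any one primary suffices.** For k independent tests at 0.05 with no true effect on any of them, the chance of at least one false positive is 1 − 0.95^k.

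- k = 2: 1 − 0.9025 = 9.75%
- k = 3: 1 − 0.8574 = 14.3%

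The outcomes are probably positively correlated. Simulating equally correlated normal test statistics (1,000,000 draws per setting) gives:

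| Correlation | 2 tests | 3 tests |
|---|---|---|
| 0.3 | 9.5% | 13.6% |
| 0.5 | 9.1% | 12.5% |
| 0.7 | 8.4% | 10.9% |

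Every entry exceeds 5%.

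**3. Error rate and power if all primaries are required.** The chance that all are falsely significant cannot exceed 5%, and with three independent tests and no true effects it is 0.05³ = 0.0125%. Alpha is safe. Power to win on all is at most that of the weakest outcome. As an illustration only, three independent outcomes with 80% power each would give 0.8³ = 51%, and two would give 0.8² = 64%. The article gives power for one.

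**4. Cost of dividing alpha instead.** Bonferroni over three tests puts 0.05 / 3 = 0.0167 on each; if they are independent, the overall error is 1 − (1 − 0.0167)³ = 4.9%. At the back-solved difference of 1.08 with 14.4 completers per arm, COPM power falls from 80% to about 64%. Restoring 80% needs about 20 completers per arm, and 20 / 0.60 = 33.3, so 34 recruited per arm instead of 24.

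**5. A single ranked primary.** One COPM test at 0.05 keeps the error at 5%, and the stated power and N = 48 still apply. Later tests made only after the preceding one succeeds do not raise the overall error above 5%.

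**The case against.** The strongest defence has four parts.

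- **Multiplicity belongs in an analysis plan.** A testing procedure and a decisive visit are commonly left to an analysis plan or full protocol that is not shown here. This stands for the visit and the procedure: their absence is not itself the fault. It does not settle which outcomes are primary and on which of them the trial is powered. The article addresses both and leaves them unreconciled.
- **The sample-size wording may mean the primary measure of one domain.** It can be read as the main instrument for everyday performance rather than the trial's only primary outcome, and sizing a trial on one of several primaries is common. That reading is fair. It removes the literal contradiction but leaves the other primaries unranked and without stated power.
- **The hypothesis may require both outcomes.** If everyday performance and length of stay must both improve, there is no inflation. The text does not say so, and the 80% would then not be the trial's power.
- **Separate tests at 0.05 are inferred.** The threshold is general, and the only outcome analysis described is the repeated-measures ANOVA. Length of stay is one value per man and does not fit it. It is therefore an inference that each primary gets its own 0.05 test.

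A reader might go further and infer an error rate of 14% to 23%. The upper end is 1 − 0.95⁵ = 22.6%. It needs five independent tests, with COPM satisfaction counted as primary and discipline and lateness counted as separate endpoints. The article names everyday performance, describes satisfaction only as something the instrument collects, and mentions discipline and lateness in parentheses.

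A reader might also compute power for length of stay by treating the 40% dropout allowance as departures from the therapeutic community. The documents do not equate the two, the Background cites community dropout of up to 71%, and no hazard-ratio analysis is planned. Such figures are not relied on here.

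**Conclusion.** The concern holds in a limited form. Three outcomes have equal primary status, one threshold applies, no success rule is fixed, and the sample size supports only the COPM.

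If any one outcome suffices, the chance of a false primary success is at most about 14% for three independent tests, about 11% to 14% for three at correlations of 0.7 down to 0.3, and about 10% for two independent tests. It is higher only if component scores are also tested separately as primaries, which the article does not state. If all outcomes are required, the 5% holds and the loss is in power.

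These figures rest on two-sided tests, no true effect on any outcome, and an assumed success rule. They bound what the text permits and are not the trial's known error rate. On either reading, the stated 80% power and 5% error do not describe a trial with three primary outcomes.

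**What to change.** Name one primary outcome: the difference between F-CaST and standard care in the COPM performance score, in line with the sample size section, at one visit. The sponsor should fix that visit before unblinded data are seen. T2 (post-intervention) is a reasonable choice, but the sample size section names no visit, so it cannot be presented as the one the calculation assumed.

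Make length of stay and then behavior key secondary outcomes, tested in that order at 0.05, each only if the preceding test is significant. Behavior must be a single defined measure for this sequence to hold 5%. Report COPM satisfaction and the remaining visits as supportive, with 95% confidence intervals. Bring the abstract, aims, primary-outcome section and registry entry into agreement.

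The cost is wording only, and N stays at 48. The downside is that a positive result on length of stay or behavior alone could no longer be claimed as confirmatory. If the sponsor will not accept that, it can require both hypothesized outcomes or divide alpha. Either choice then needs its own power statement, and dividing alpha three ways would need about 34 recruited per arm to keep 80% for the COPM under the assumptions above.
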